### Qualitative site visits

SPARC researchers will visit each participating intervention and control practice to assess practice organizational characteristics and workflow related to care of patients with diabetes. Site visits will be conducted at three points during the study: at baseline, 12 months, and 24 months.

Researchers will use four primary methods for data collection during the site visits: participant observation, key informant interviews, cost survey instruments, and semistructured clinician interviews. Participant observations will consist of three to four observation periods in each practice, each period lasting 3 to 5 h. Observations will be guided by an observational template developed during the R34 pilot study and refined for use in this project. SPARC researchers will observe practice workflow, care delivery, and check-in processes, with special attention paid to diabetes-specific and registry-specific activities. During observations, researchers will identify two or three practice members for interviews to learn more about workflow changes in registry implementation. Qualitative site visits will also include interviews with practice managers or administrators to collect cost data relevant to registry implementation.

### Measuring registry cost

To estimate cost-effectiveness of the registry, we will compare costs experienced by intervention and control practices. At the 12- and 24-month site visits, SPARC researchers will collect practice-level ongoing operational costs in treating patients with diabetes. The instrument records the amount of time that clinicians, nurses, and office staff spend on patient encounters, chart reviews, and reports.

In addition to operational costs, the registry may entail start-up costs to practices. We will measure start-up costs, including purchases, staff training time, identification of patients for inclusion in a registry, and data entry during the baseline site visits. We will measure costs associated with use of peer mentors and physician informaticists by reviewing their activity logs.

We will estimate the dollar value of time spent by office staff and peer mentors using average wage rates by occupation, in Virginia, from the US Bureau of Labor Statistics.

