### Setting and recruitment

The intervention will target 30 Virginia internal medicine and family medicine practices participating in the Virginia Ambulatory Care Outcomes Research Network (ACORN) [41]. ACORN, sponsored by VCU, is a practice-based research network of nearly 100 primary care practices. Member practices are in rural, urban, and suburban settings and range from single-clinician practices to large practice groups and hospital-owned clinics. ACORN member practices choose which studies to be involved in and receive no specific benefit as part of their membership, other than the opportunity to contribute to advancing the science of primary care.

Practices eligible to participate in SPARC must meet the following criteria: (1) the practice must treat adult patients with type 2 diabetes, (2) the clinicians and staff in the practice must be able to change workflows in support of the intervention, and (3) the practice must have a clinician champion who can attend champion meetings (described below) and lead registry implementation in the practice. Practices already using a registry or those that do not currently use an EHR are excluded from participation.

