### Peer mentors and physician informaticists

Peer mentors, available only to the intervention practices, are practicing clinicians who have successfully implemented and maintained a diabetes registry in their practice. The peer mentors will attend the first champion meeting for intervention practices to present information on registry development and answer questions about it. After the meeting, clinician champions from intervention practices will be paired with a peer mentor who will advise them on the use of the self-assessment tool and will offer basic guidance regarding workflow redesign. Peer mentors will visit each intervention practice at least twice during the first study year: once at baseline and once shortly after the practice begins using the registry. In between these visits, peer mentors will call practice-level champions in the intervention practices monthly to monitor implementation progress, offer assistance, and help the practice connect to basic technical assistance from the physician informaticist if needed. Practice-level champions can contact the peer mentors by telephone or email throughout the intervention period.

Some practices will be able to adopt registries successfully with little additional support; others may need some limited technical assistance or guidance. Peer mentors will tailor their efforts to specific practice situations to meet these varied needs. The mentors’ decisions regarding the need for additional in-person visits or more frequent telephone contact will be guided by the SPARC Milestones document, which outlines eight critical steps in the meaningful adoption of a diabetes registry (see Additional file 1). This document will also be shared with intervention practices during the first champion meeting. Peer mentors will use this document to assess monthly implementation progress for each intervention practice and determine whether a specific practice needs additional support.

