### Data collection

SPARC researchers will collect data using mixed-methods explanatory sequential design [43]. In such a design, data collection happens in iterative cycles during which preliminary findings from one set of data influence data points collected in the next set of data. For example, findings during a chart audit review might identify the need for collection of qualitative data elements not previously identified, so that the significance of chart audit findings might be better understood. Data collected in SPARC will include medical record review, cost data, participant observations, key informant interviews, and in-depth interviews with practice champions and project leads [44]. Data collection will occur at baseline, 12 months post-registry implementation, and 24 months post-registry implementation. We understand it is possible that not all practices will successfully implement a diabetes registry and that some control practices may implement a registry without assistance. Based on our findings from the R34 pilot study, initial adoption of a registry will take up to 3 months. We will use medical record reviews (described in the next section) to collect patient outcome data (mainly hemoglobin A1c) with which we will evaluate the effectiveness of the registry. Data collected during qualitative site visits (described below) will allow SPARC researchers to evaluate the contextual factors and practice characteristics associated with successful implementation of a diabetes registry, including any barriers or problem-solving strategies that practices employ to enable registry implementation. During qualitative site visits, we will also collect information related to cost of the intervention in each practice.

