### Trial status

Recruitment was conducted February to November 2014, with 30 practices currently enrolled in SPARC. The first champion meeting for control practices is scheduled to take place in March 2015, and we anticipate starting baseline data collection activities at that time. The first champion meeting for intervention practices will be held soon thereafter, with baseline data collection for that group beginning immediately after. Baseline data collection for control and intervention groups will be completed by June 2015. Data cleaning and analysis of preliminary baseline data will begin soon after baseline collection is complete.

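### Registry start-up costs are assigned to the baseline visit, before most of them arise, so practice-borne start-up cost is likely to be under-counted in the cost-effectiveness ratio

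*Protocol article*

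**What the plan says.** All places are in the protocol article.

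- **Measuring registry cost** places the measurement of "start-up costs, including purchases, staff training time, identification of patients for inclusion in a registry, and data entry during the baseline site visits". For operating cost it says: "At the 12- and 24-month site visits, SPARC researchers will collect practice-level ongoing operational costs in treating patients with diabetes". That instrument records staff time on encounters, chart review and reporting. Mentor and informaticist costs come from activity logs.
- **Setting and recruitment**: "Practices already using a registry or those that do not currently use an EHR are excluded from participation".
- **Data collection**: on pilot experience, "initial adoption of a registry will take up to 3 months". The follow-up points are counted from registry implementation. The section also says, without naming a visit, that site visits will gather information on intervention cost.
- **Peer mentors and physician informaticists**: mentors visit at least twice in the first year, "once at baseline and once shortly after the practice begins using the registry".
- **Trial status**: the intervention group's first champion meeting follows the control group's, which is set for March 2015, "with baseline data collection for that group beginning immediately after". "Baseline data collection for control and intervention groups will be completed by June 2015".
- **Qualitative site visits** (baseline, 12 and 24 months): "Qualitative site visits will also include interviews with practice managers or administrators to collect cost data relevant to registry implementation".
- **Cost analysis**: the ratio divides the between-arm difference in intervention costs by the between-arm difference in outcomes. The components of the numerator are not listed.

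**The concern.** Buying software, training staff, finding patients and entering their data are how a practice gets a registry. A visit held before or at the very start of that work cannot record what it will cost. The later visits do not obviously pick it up, because the instrument described for them measures routine running time.

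Aim 3 is the cost and cost-effectiveness of the intervention, and low cost is central to the case for the trial. The article intends to tell other practices what a 0.5 percentage point reduction in mean A1c costs. A practice deciding whether to adopt would want the start-up cost in that figure. If it is under-counted, mainly in the arm that is being helped to adopt, the ratio will tend to look too good.

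A lesser point is that operating cost has no baseline value, although A1c is analysed as change from baseline.

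**Working it through.** The documents contain no cost mean, standard deviation or total, so there is no planned figure to reproduce. The main check compares timings.

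**1. What has happened by the baseline visit?**

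| Step | Timing in the article |
|---|---|
| Entry | No practice is using a registry (exclusion criterion) |
| First champion meeting | Practices learn about registries, software options and what to raise with the EHR vendor; intervention practices meet their mentors and the informaticist |
| Baseline visit, intervention arm | Begins immediately after that meeting; all baseline work is done by June 2015 |
| Adoption | Takes up to 3 months |
| Second mentor visit | Shortly after registry use begins, and distinct from the baseline visit |

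Baseline therefore falls before adoption or early in it. Purchases, training and data entry would be largely unincurred. Patient identification is the item most likely to have started, because both arms must list their type 2 diabetes patients for chart review. For that reason it may largely cancel in a between-arm difference.

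**2. Does the later instrument cover the gap?** As described, it records time on encounters, chart review and reports. It does not mention purchases, training or initial data entry. The activity logs cover mentors and informaticists, not the practice's own spending and staff time.

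**3. Effect on the ratio.** Let S be practice-borne start-up cost, O operating cost and M the logged mentor and informaticist cost, with subscripts I and C for the arms. If all components enter,

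numerator N = (S_I − S_C) + (O_I − O_C) + M.

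If a fraction m of start-up cost is missed in both arms, N falls by m(S_I − S_C), a relative understatement of m(S_I − S_C)/N. With N positive, the ratio is too favourable when S_I exceeds S_C. That is expected, since the intervention exists to promote adoption, but control practices that start a registry unaided shrink the effect. None of m, S, O or M is given, so the size cannot be computed.

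**4. Baseline operating cost (illustration).** Take one cost value per practice, n practices per arm, and an assumed correlation ρ between baseline and follow-up cost. Standard errors of the between-arm difference, in SD units:

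- follow-up only: √(2/n)
- baseline as covariate: √(2/n) × √(1 − ρ²)
- raw change: √(2/n) × √(2(1 − ρ))

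For n = 15, √(2/15) = 0.365. At ρ = 0.5 the covariate form gives 0.365 × √0.75 = 0.316.

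| n per arm | ρ (assumed) | Follow-up only | Covariate | Raw change |
|---|---|---|---|---|
| 15 | 0.3 | 0.365 | 0.348 | 0.432 |
| 15 | 0.5 | 0.365 | 0.316 | 0.365 |
| 15 | 0.8 | 0.365 | 0.219 | 0.231 |
| 12 | 0.3 | 0.408 | 0.389 | 0.483 |
| 12 | 0.5 | 0.408 | 0.354 | 0.408 |
| 12 | 0.8 | 0.408 | 0.245 | 0.258 |

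The n = 12 rows take the allowed loss of six practices as evenly split. A baseline value used as a covariate improves precision throughout this range. A raw change score loses precision when ρ is below 0.5.

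**The case against.** The strongest reply is that the article commits to measuring start-up costs and provides for cost data more widely than its costing section suggests. Qualitative site visits lists cost survey instruments among its methods and adds manager or administrator interviews on implementation cost. Data collection speaks of intervention cost at site visits. Neither is limited to baseline. Intervention baseline visits follow the champion meeting and could run towards June 2015, so a late visit might catch some early work. Purchases may also be modest, since certified EHRs must offer registry functions and free software is available otherwise.

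Much of this stands, and it limits the point in three ways.

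- A reader might infer that start-up cost is omitted altogether. The documents do not support that. They leave room to collect it later, and Cost analysis does not exclude it. But the general statements name neither the items nor the visit, while the specific section names both and chooses baseline.
- A reader might infer that the operating-cost comparison is biased or will be unadjusted. Randomization, stratified on setting, size and ownership, keeps a follow-up-only difference unbiased in expectation. The article is silent on cost adjustment, which may be left to an analysis plan.
- A reader might suppose that start-up is, say, 25–60% of first-year practice cost and conclude that the ratio is understated by as much. The documents give no such share, and a share of practice cost does not carry over one for one to a between-arm numerator that also holds logged mentor cost.

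The reply does not show that the visit named for start-up costs is one at which they can be measured.

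**Conclusion.** The point holds as a timing fault in the costing section. Followed as written, it would largely miss or under-count practice-borne start-up cost, and the cost-effectiveness ratio would tend to be too favourable. The direction assumes more start-up activity in the intervention arm and a positive cost difference. The amount cannot be quantified from the documents. The conclusion also rests on reading the costing section as governing over the general remarks on site visits, and the two need reconciling.

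The missing baseline for operating cost is secondary. It costs precision and leaves chance imbalance between 15 and 15 practices uncorrected, but it is not a bias. Under the assumed correlations, 15 practices per arm and a covariate analysis, the standard error would fall from 0.365 SD to between 0.348 and 0.219 SD.

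This should be fixed. It concerns Aim 3 only; the primary A1c comparison and its power are unaffected.

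**What to change.** 1. Amend Measuring registry cost so that start-up costs are collected after adoption: at the existing 12-month visit, and at 24 months for late adopters, for every practice in either arm that started a registry. The recall period would run from baseline to first registry use.
2. Reconcile Data collection and Qualitative site visits with this by naming which cost items are collected at which visit.
3. State in Cost analysis that start-up costs enter the numerator, alongside operating and logged mentor and informaticist costs.
4. As a secondary improvement, give the existing operating-cost instrument at the baseline visit as well, and use baseline cost as a covariate rather than analysing raw change.

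No new visits are needed. The costs are some recall error in start-up time and spending, and extra interview time with practice managers. When the article was written baseline collection was still ahead, so item 4 was then feasible. If that visit has passed, items 1 to 3 can still be done, but a baseline operating cost cannot be recovered reliably.

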### Outcomes

#### Statistical analysis

We will assess intervention effectiveness by comparing the change in patient-level hemoglobin A1c scores from baseline to year 1 between intervention and control practices. A linear mixed-effects model will be used to account for the continuous repeated-measure response (A1c), a fixed-effect group indicator (two levels: intervention, control), a fixed-effect time indicator (two levels: baseline, year 1), and an interaction of the group and time indicators. A practice-level random effect will be included to account for intracluster correlation. Any adjustments to this model for patient- or practice-level characteristics will be made by including those measures as fixed effects. We will analyze secondary effectiveness measures using similar linear mixed-effects models of numerical and categorical measurements, including whether diabetes patients met targets for blood pressure control or LDL cholesterol.

We will assess intervention maintenance of the change in A1c scores using a similar model, with the time periods changing to baseline and year 1, and year 1 to year 2. We will assess practice-level implementation and maintenance using *t*-tests for unadjusted comparisons and using analysis of covariance to adjust differences for practice characteristics. We will categorize practices according to their allocated group, regardless of compliance (intention-to-treat analysis) [45].

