### Randomization

To ensure a balance between the intervention and control groups of practices on the key practice characteristics of setting (rural or urban), size (fewer than three, versus three or more, clinicians), and ownership type (independent or group), the 30 practices were divided into the eight strata formed by these three characteristics and then randomized with equal probability between intervention and control using a random number generator, with 15 practices allocated to the intervention group and 15 to the control group. Each practice was assigned a study identification number upon allocation. Once a year, participating practices will provide the SPARC research team with the total number of adult patients with type 2 diabetes in their practice. Using that number as an upper threshold, a biostatistician on the SPARC research team will generate 100 random numbers for each practice. This number list will be used to identify 100 patient medical records for review in each practice.

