### Sample size and power analysis

For evaluating intervention effectiveness, we will review 100 patient records in each of the 30 practices at baseline and 1- and 2-year follow-up intervals. We will draw independent random samples of patient records for each of these reviews, and data will be recorded without patient identifiers. Because patients are not recruited and are not the subjects of the intervention, patient dropout is not a significant issue.

The primary outcome variable is patients’ hemoglobin A1c levels. The research team obtained data on patient hemoglobin A1c levels from practices that participated in the R34 pilot, finding a mean of 7.1, a standard deviation of 1.6, and an intraclass correlation coefficient of 0.065, providing 80% power to detect a 0.5-level decrease in mean hemoglobin A1c from baseline to 1 year in the intervention arm as opposed to the control arm, allowing for up to 20% or six of the participating practices to drop out. If fewer practices drop out of the study, we will have 80% power to detect 15% improvement in the percentage of patients with LDL < 100 (from 53% at baseline to 61% at follow-up), a 20% increase in the percentage of patients with BP < 130/80 (42.2% baseline, 50.6% follow-up), and a 25% increase in the percentage of patients in each practice with HbA1c < 7 (59.2% to 74%). The anticipated baseline rates for these outcomes are derived from baseline rates observed in the pilot study practices.

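### The primary model names one practice-level random effect for unlinked samples at two times, so the group-by-time test omits practice-specific drift and its type I error can exceed 5%

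*Protocol article*

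**What the plan says.** The Statistical analysis section of the Protocol article assesses effectiveness by the change in A1c from baseline to year 1 between arms. The fixed part of the linear mixed model has a group indicator, "a fixed-effect time indicator (two levels: baseline, year 1), and an interaction of the group and time indicators". The random part is given in one sentence: "A practice-level random effect will be included to account for intracluster correlation". Adjustments for patient or practice characteristics enter as fixed effects. The secondary effectiveness measures, and maintenance of the A1c change, use similar models. The section calls A1c a repeated-measure response.

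The Sample size and power analysis section describes the data: "We will draw independent random samples of patient records for each of these reviews, and data will be recorded without patient identifiers". It also says "we will review 100 patient records in each of the 30 practices at baseline and 1- and 2-year follow-up intervals". Under Randomization the practices are the allocated units, "with 15 practices allocated to the intervention group and 15 to the control group".

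**The concern.** The treatment effect is the group-by-time interaction. A practice effect that is constant over time cancels from each practice's change, so it contributes nothing to the error of that contrast. Two sources of error remain: sampling of patients, and how differently practices move from baseline to year 1. The model as worded has a term only for the first. Patients cannot be linked, so the data offer no other repeated unit to carry the second.

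With 100 records per practice at each time, patient sampling error in a practice mean is small, and even modest practice-specific drift is large beside it. Practices can drift for reasons unrelated to the intervention. The article itself describes changing EHR capability and payment arrangements, and expects that some control practices may adopt a registry unaided. If such drift exists, the primary confidence interval is too narrow and ordinary practice change could be read as an intervention effect.

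**Working it through.** **Inputs from the Protocol article.** SD 1.6 (variance 2.56), ICC 0.065, m = 100 records per practice per time, and J = 15 practices per arm. J is 12 if six practices are lost, taken as three per arm ("allowing for up to 20% or six of the participating practices to drop out"). Between-practice variance is 0.065 × 2.56 = 0.1664. Within-practice variance is Ve = 2.56 − 0.1664 = 2.3936.

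**Assumptions.** Two-sided alpha 0.05. CAC, the share of practice variance that is stable from baseline to year 1, is varied from 1 to 0.5. No patient is drawn at both times (relaxed below).

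**The plan's own power figure.** The design effect is 1 + 99 × 0.065 = 7.435. With 12 practices per arm the effective size is 1,200/7.435 = 161.4 per arm, SE = 1.6 × √(2/161.4) = 0.178, and power for a difference of 0.5 is 80.2%. The stated 80% is reproduced, but by a comparison at a single time point that carries the full practice variance. The planned group-by-time model, if its zero-drift assumption were true, would have SE = √[(2/12)(2 × 2.3936/100)] = 0.089. Its detectable difference would be 0.25 and its power for 0.5 above 99.9%. So the power statement and the analysis model do not rest on the same error term.

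**True and reported standard errors.**
- Practice-by-time variance: Vpt = (1 − CAC) × 0.1664.
- True variance of the interaction estimate: (2/J)(2Ve/m + 2Vpt).
- Variance reported by the model as worded: (2/J)(2s²/m). Here s² pools the within-cell variation (99 × 60 = 5,940 df) with the practice-by-time variation (28 df).
- Type I error = 2[1 − Φ(1.96 × reported SE / true SE)].

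**Worked case, J = 15, CAC 0.8.** Vpt = 0.0333. The practice-by-time mean square is 2.3936 + 100 × 0.03328 = 5.72. The pooled s² is 2.3936 + 28 × 3.328/5,968 = 2.41. The SE ratio is √(5.72/2.41) = 1.54, and the type I error is 2[1 − Φ(1.96/1.54)] = 20.3%.

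| CAC | Practice-by-time SD (A1c points) | True SE | Reported SE | Type I error |
|---|---|---|---|---|
| 1 | 0 | 0.080 | 0.080 | 5.0% |
| 0.95 | 0.091 | 0.093 | 0.080 | 9.1% |
| 0.9 | 0.129 | 0.104 | 0.080 | 13.2% |
| 0.8 | 0.182 | 0.124 | 0.080 | 20.3% |
| 0.7 | 0.223 | 0.140 | 0.080 | 26.2% |
| 0.5 | 0.288 | 0.169 | 0.081 | 35.0% |

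Twelve practices per arm give the same error rates. Simulation of the same statistics (20,000 replicates per setting) agrees, for example 20.3% at CAC 0.8 and 34.6% to 35.2% at 0.5. Random-intercept mixed models fitted to 381 simulated trials per setting gave 4.2% at CAC 1, 15.2% at 0.9 and 24.1% at 0.8. A smaller run of 150 gave 10% at CAC 1 and 18% at 0.8. Pooled, that is (16 + 15)/531 = 5.8% and (92 + 27)/531 = 22.4%, which agrees with the formula within simulation error of about 1 to 2 points.

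**Allowing for overlap.** If a fraction f of the sampled patients appears at both times with within-patient correlation r, the term 2Ve/m becomes (2Ve/m)(1 − f·r). Neither f nor r is in the article. For f = 0.2 to 0.5 and r = 0.5 to 0.7, f·r runs from 0.10 to 0.35.

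| CAC | Type I error, f·r from 0.35 to 0.10 |
|---|---|
| 1 | 1.5% to 3.9% |
| 0.95 | 5.0% to 7.9% |
| 0.9 | 9.1% to 12.0% |
| 0.5 | 33% to 35% |

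**After correction.** A t-test on practice-level changes gives a simulated type I error of 4.7% to 5.2% at every CAC tried, with 22 or 28 df.

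**The case against.** The strongest reply is that this is a condensed article. It says neither that the practice effect is the only random effect nor that it is an intercept, and an analysis plan that is not shown could add a time-varying term. That is possible. But the article does state the random part, and its plain reading is one time-constant effect.

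Other points on that side stand and limit the finding:

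- A reader might infer from the independent samples that no patient is measured twice. The article does not support that. The draws are made from the same practice's patient list at each review, and some practices have fewer than three clinicians, so the same patient can be drawn again. The samples are unlinked, not disjoint. Overlap reduces the true variance, so the error rates without overlap are upper figures at each CAC.
- A reader might infer a definite type I error such as 20%. No CAC or practice-by-time variance is stated, so the result is a range that starts at no inflation.
- The article's interest in practices' varied responses to the intervention is not evidence of drift under the null hypothesis, and I do not rely on it.
- The degrees of freedom matter little by themselves. With a practice-by-time term but a normal reference, the error is about 6%.
- The effect on the binary secondary outcomes was not computed. The practice-level t-tests and analyses of covariance for implementation and maintenance are not affected.
- The 80% power figure keeps the full practice variance, so the trial was not sized on the small standard error.

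**Conclusion.** The concern holds as a conditional one. As worded, the primary model leaves practice-by-time variance out of the group-by-time test. The type I error exceeds 5% when practices drift differently between baseline and year 1 and chance patient overlap does not offset this.

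The direction is secure. The size is not, because it rests on an unstated CAC. A practice-by-time SD of 0.13 A1c points (CAC 0.9) is enough to give about 13% without overlap, or 9% to 12% with the overlap assumed above. Because this is the primary test, the error is anti-conservative and the correction is cheap, it should be settled before the data are analysed.

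**What to change.** Add a random practice-by-time effect to the primary A1c model and to the similar secondary and maintenance mixed models. For the linear models, test group-by-time with Satterthwaite or Kenward-Roger degrees of freedom. For the primary outcome, a simple equivalent is a t-test on the practice-level mean changes, with 28 df if all 30 practices remain. Its error comes from the observed spread of those changes, so it also allows for patient overlap. Describe the data as repeated cross-sectional samples, with the change being in the practice mean, and restate power for this test with an assumed CAC.

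The cost is a sentence of model wording, one more variance component and wider confidence intervals. Power for a 0.5 difference (normal approximation, no overlap) would be 98.2% at CAC 0.8 and 84.1% at 0.5 with 15 practices per arm, or 95.2% and 75.4% with 12. If practices do not drift, it stays above 99.9%. The Trial status section places baseline collection still ahead, so the change can be fixed before outcome data exist.

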## Abstract

**Background:**

Diabetes is predicted to increase in incidence by 42% from 1995 to 2025. Although most adults with diabetes seek care from primary care practices, adherence to treatment guidelines in these settings is not optimal. Many practices lack the infrastructure to monitor patient adherence to recommended treatment and are slow to implement changes critical for effective management of patients with chronic conditions. Supporting Practices to Adopt Registry-Based Care (SPARC) will evaluate effectiveness and sustainability of a low-cost intervention designed to support work process change in primary care practices and enhance focus on population-based care through implementation of a diabetes registry.

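### The A1c maintenance analysis names only adjacent-period contrasts; the baseline-to-year-2 difference between arms, the direct measure of a sustained effect, is not named

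*Protocol article*

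**What the plan says.** The abstract's Background paragraph says the study "will evaluate effectiveness and sustainability of a low-cost intervention". Under Sample size and power analysis, "we will review 100 patient records in each of the 30 practices at baseline and 1- and 2-year follow-up intervals", and "We will draw independent random samples of patient records for each of these reviews". Table 1 limits peer mentoring to the first 12 months, so year 2 shows what remains once mentoring has ended.

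The primary model in Statistical analysis has a group indicator, "a fixed-effect time indicator (two levels: baseline, year 1), and an interaction of the group and time indicators". For clustering, "A practice-level random effect will be included to account for intracluster correlation". On maintenance the text reads: "We will assess intervention maintenance of the change in A1c scores using a similar model". The same sentence then sets out which periods that model compares: "with the time periods changing to baseline and year 1, and year 1 to year 2". The next sentence plans t-tests and analysis of covariance for practice-level implementation and maintenance, but names no contrast of year 2 with baseline for A1c.

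**The concern.** An effect is sustained if the arms still differ, relative to baseline, at year 2. Of the two contrasts named, the first repeats the primary analysis and the second asks whether the arms moved apart or together after year 1. Neither is the quantity of interest by itself.

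The second contrast is the one a reader would turn to for maintenance, and its null hypothesis is no further change. Failure to reject that null is not evidence that the effect has been kept, particularly when the contrast is imprecise. What is at stake is the claim anticipated in the Discussion, that the approach can be effective and sustainable. The plan should produce one estimate with an interval that bears on that claim.

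**Working it through.** **Inputs from Sample size and power analysis and Randomization.** The pilot gave "a mean of 7.1, a standard deviation of 1.6, and an intraclass correlation coefficient of 0.065". There are 100 records per practice per review, 15 practices per arm, and an allowance for losing six practices (taken here as 12 left per arm). The article's target is 80% power for a difference of 0.5.

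**Assumptions.** Two-sided alpha of 0.05; equal loss of practices between arms; and r, the correlation of a practice's effect between periods, equal for every pair of periods. The article does not give r, so it is varied from 0 to 1.

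**1. The article's own power figure.** The design effect is 1 + 99 × 0.065 = 7.435. The SE of a two-arm difference is 1.6 × √(2 × 7.435 / 1200) = 0.178. Then 0.5 / 0.178 = 2.81, which gives power of 80.2%. The stated 80% is reproduced, as a comparison of two arms at one time point.

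**2. How the contrasts relate.** Let d0, d1 and d2 be the differences between arms at baseline, year 1 and year 2. Then (d1 − d0) + (d2 − d1) = d2 − d0. A simulation with true effects of −0.5 at year 1 and −0.25 at year 2 gave mean contrasts of −0.50, +0.25 and −0.25, and the first two summed exactly to the third. Because d1 enters both planned contrasts with opposite sign, they are negatively correlated (−0.50 in the simulation). Adding their variances as if they were independent would inflate the SE of the sum by √2. At r = 0.8 with 12 practices per arm, that is 0.138 × 1.41 = 0.195 in place of 0.138.

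**3. Precision of the year-1-to-year-2 contrast.** With k practices per arm,

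Var = 2 × 1.6² × [2(1 − 0.065)/100 + 2 × 0.065 × (1 − r)] / k.

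At k = 12 and r = 0.8 this is 5.12 × (0.0187 + 0.026) / 12 = 0.0191, so SE = 0.138. The probability of a non-significant result when the true late change is δ is 1 − [Φ(δ/SE − 1.96) + Φ(−δ/SE − 1.96)]. Loss of half of a 0.5 effect is δ = 0.25; loss of all of it is δ = 0.5.

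| r | SE, 12 per arm | Half lost, non-significant | All lost, non-significant | SE, 15 per arm | Half lost, non-significant |
|---|---|---|---|---|---|
| 1 | 0.089 | 20% | about 0% | 0.080 | 12% |
| 0.8 | 0.138 | 56% | 5% | 0.124 | 47% |
| 0.5 | 0.189 | 74% | 25% | 0.169 | 68% |
| 0 | 0.252 | 83% | 49% | 0.225 | 80% |

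At the SE of 0.178 implied by the article's own power statement, the two 12-per-arm probabilities would be 71% and 20%.

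**4. Precision of the contrast that is missing.** Under the same assumptions the baseline-to-year-2 contrast has the same SE as each adjacent contrast. With 12 practices per arm its 95% CI half-width is 1.96 × SE: 0.175 at r = 1, 0.271 at r = 0.8 and 0.494 at r = 0.

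**The case against.** A reader might infer that the plan can never estimate the effect remaining at year 2. The text does not support that. The point estimate is the sum of the two named contrasts, and the wording (one similar model, several periods) is compatible with a single three-time-point fit, which would also give the standard error. What stands is that the primary model's time factor has two levels, so changing its periods reads most naturally as two separate fits, and those do not supply the standard error.

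A reader might also infer that a non-significant late change will be declared maintenance, or that maintenance could be claimed with no year-1 effect. The article states no such rule. A criterion could sit in an analysis plan that is not shown, and the absence of one here is no fault. The baseline-to-year-1 contrast would also show whether there was anything to maintain.

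The size depends heavily on r. Under the practice-only random effect that the article writes down (r = 1), the late contrast has about 80% power for a 0.25 loss, and even at r = 0.8 complete loss is missed only 5% of the time. Finally, sustainability is not among the four formal aims, the primary analysis stops at year 1, and 24-month qualitative visits add further evidence. These points limit the importance of the concern. They do not supply the missing contrast.

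**Conclusion.** The point holds in a limited form. The article fixes the A1c maintenance contrasts as two adjacent periods and leaves unnamed the baseline-to-year-2 difference between arms, which answers the sustainability question directly. The later of the two contrasts is weak evidence of maintenance by itself unless practice effects are nearly constant over time. With 12 practices per arm, a loss of half of a 0.5 effect would be non-significant between 20% (r = 1) and 83% (r = 0) of the time. That range rests on the pilot SD and intraclass correlation, an equal split of lost practices, two-sided 0.05, an assumed r that is the same between all periods, and a test whose standard error is right for that r. The primary year-1 comparison is not affected.

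**What to change.** Replace the maintenance sentence with one that specifies:

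- one linear mixed model fitted to all three samples, with a three-level time factor and group-by-time interaction;
- the baseline-to-year-2 group-by-time contrast, with its 95% CI, as the maintenance estimate;
- the year-1-to-year-2 contrast, with its CI, as a supporting estimate.

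A practice-by-time random effect is advisable, because the standard error depends on how much practice effects shift between periods (0.089 at r = 1 against 0.252 at r = 0). Its small downside is wider intervals.

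The cost is a sentence or two of analysis text and, if the random effect is added, a change to the stated error structure. No data are needed beyond the year-2 reviews already planned. According to Trial status, baseline collection was still to begin, so the change could be made before any outcome data were seen.
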